### Data Collection Quality Control

The following measures are implemented for user-related issues: (1) noncompliance: participants with missing data for >20% of nights are excluded and replaced; (2) charging issues: backup chargers are provided, and daily battery monitoring is required; (3) unauthorized modifications: settings are locked, and violations lead to replacement; and (4) sync delays: daily commitment for cloud backup within 24 hours. The following measures are implemented for device-related issues: (1) fragmented recording: nights without combined scores are excluded; (2) data mismatch: nights with artifact conflicts are excluded; and (3) sync errors: multiple attempts are made with escalating intervals. For sensor inaccuracies, quality control is performed through sleep diaries, and outliers trigger replacement. Excluded participants are replaced from the recruitment pool to maintain the sample size. The expected night exclusion impact is around 18%, with anticipated replacement ensuring the target sample.

Subjective data collection is performed through PSQI forms completed on paper. Information is manually entered by the researcher into a password-protected spreadsheet with self-verification (data are entered twice by the researcher to ensure accuracy). Data are processed through the manufacturer’s algorithms to interpret the findings of the 10 explanatory variables and the target variable (Table 1).

**Table 1. T1:** Target and explanatory variables collected by the wearable (indispensable for this study).

Variable		Description	Unit	Data type
Explanatory variable				
sleep_duration		Sum of N1, N2, N3, and REM^a^	Minutes	Integer
movement_awakening		Count of movement during sleep	Number	Integer
sleep_cycle		Count of sleep cycles	Number	Integer
mental_recovery		Score assigned according to the REM phase	Score (0‐100 scale)	Integer
physical_recovery		Score assigned according to the N3 phase	Score (0‐100 scale)	Integer
efficiency		real_total_sleep by sleep_duration	Percentage	Integer
Transition_N1		Sum of minutes of sleep in the N1 phase	Minutes	Integer
Light_N2		Sum of minutes of sleep in the N2 phase	Minutes	Integer
Deep_N3		Sum of minutes of sleep in the N3 phase	Minutes	Integer
REM		Sum of minutes of sleep in the REM phase	Minutes	Integer
Target variable				
sleep_score		Score assigned for the night	Score (1‐100 scale)	Integer

a REM: rapid eye movement.

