### Adherence Assessment

In the experimental group, adherence to personalized recommendations is assessed through self-report at the day 60 closure interview. Participants rate adherence on a scale from 0% to 100% for each recommendation provided. In the control group, adherence to generic sleep hygiene is assessed in a similar manner. Device wear adherence is monitored through objective data. Participants with missing data for >20% of nights may be excluded and replaced.

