### Sample Size: Pilot Feasibility Justification

This pilot trial enrolls 32 participants (16 per arm; stratified by sex), and this is consistent with established pilot study guidelines recommending 12‐15 participants per arm for feasibility assessment [117-120]. The sample size is explicitly designed for pilot objectives, not definitive efficacy testing.

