### Pilot Objectives

The pilot objectives are as follows:

Feasibility: Can we successfully recruit, enroll, randomize, and retain participants? Can personalized ML interventions be delivered? Do participants engage with recommendations?Preliminary effect size estimation: What magnitude of difference between groups might we observe? What variability exists within groups? What baseline-to-follow-up correlation informs covariate adjustment? The estimates can inform future randomized controlled trial (RCT) sample size calculations.Methodology refinement: What challenges arise in data collection, ML model training, and intervention delivery? What proportion of nights yield usable data? Which sleep parameters show the most predictive value?Hypothesis generation: Does personalization show a promising signal warranting a larger trial? Do certain participant subgroups respond better?

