#### Exploratory Analyses: Hypothesis Generation Only

The exploratory analyses involve the following three aspects:

Individual parameter changes: Compare the change in specific sleep variables (duration, deep sleep percentage, and REM percentage) between groups using *t* tests (unadjusted for multiple comparisons, given the exploratory nature).Adherence subgroups: In the experimental group, compare outcomes between high (≥80%) and low (<80%) self-reported adherence using the Mann-Whitney *U* test.Predictive feature patterns: Perform a descriptive analysis of which sleep parameters are most frequently identified as the top predictors across participants.

All exploratory analyses are labeled hypothesis-generating, not confirmatory. No adjustments are made for multiple comparisons, given the pilot scope of the study. Regarding the handling of missing data for the primary outcome (sleep score), participants are excluded if sufficient night data are not available in the baseline and postintervention periods, and action on the secondary outcome (PSQI) is derived from the handling of the primary outcome. This protocol contains the complete statistical analysis plan, and no separate statistical analysis plan exists.

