### Access Control and Protection Layers for Potential and Excluded Participants

Data collected from potential participants who do not fill out the informed consent form (Multimedia Appendix 3) or the commitment letter (Multimedia Appendix 4) and those who voluntarily withdraw or need to be excluded from the study are immediately and securely deleted.

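### Participants are excluded and replaced after allocation with no stated analysis of all randomised participants, and deleting their data conflicts with the retention and harms aims

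*Protocol article*

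**What the plan says.** - **Timing.** Allocation Concealment Mechanism places the reveal of allocation at day 0, after the baseline PSQI and device handover. All 60 nights are recorded afterwards.
- **Exclusion and replacement.** Data Collection Quality Control: "participants with missing data for >20% of nights are excluded and replaced". Replacements come from the recruitment pool to keep the sample size. Adherence Assessment is permissive: "Participants with missing data for >20% of nights may be excluded and replaced". The quality-control section adds, for sensor inaccuracies, that "outliers trigger replacement".
- **Missing data.** Under Exploratory Analyses, the rule for the watch data is that "participants are excluded if sufficient night data are not available in the baseline and postintervention periods". The questionnaire gets no rule of its own; the article says only this about it: "action on the secondary outcome (PSQI) is derived from the handling of the primary outcome". The same section says that the protocol holds the whole statistical analysis plan and that no separate one exists.
- **Deletion.** Access Control and Protection Layers for Potential and Excluded Participants says that data of "those who voluntarily withdraw or need to be excluded from the study are immediately and securely deleted".
- **Aims that need those data.** Pilot Objectives asks "Can we successfully recruit, enroll, randomize, and retain participants", and what proportion of nights is usable. Harms: Adverse Event Tracking undertakes to report every adverse event in the final analysis.

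**The concern.** A randomised comparison is protected from selection only if people are analysed in the arm to which they were allocated. Here, membership of the analysed 32 depends on what happens after allocation: wearing the watch, syncing, and having enough scored nights. Participants who fall short leave, and others take their places.

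The critical window is days 31-60. By then the arms have received different advice, experimental participants know their group and control participants do not, and the one researcher who holds the sequence and all the data has been unblinded. If disengagement in that window is related to how well the advice works, the adjusted group difference is distorted. Tying the PSQI to watch data extends the same selection to an outcome collected on paper. A permissive exclusion rule in one section and an automatic one in another leaves room for judgement by someone who knows the arm.

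Deletion makes the problem irreversible: no sensitivity analysis can recover the outcomes of those removed. Effect size and retention are both stated pilot objectives meant to inform a larger trial, so pilot status does not make this harmless.

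**Working it through.** **1. The plan's own figures.** 32 participants × 60 nights = 1920, which matches the target. With the expected 18% of nights excluded, 1920 × 0.82 ≈ 1574 remain. Reaching 1920 usable nights would take 1920 / (60 × 0.82) = 39.0, so 40 contributors after rounding up. One-for-one replacement back to 32 reaches 1920 only if the retained participants lose no nights. The article nevertheless relies on replacement to reach that target, so replacement is an expected part of the design.

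**2. How often the 20% cut could be crossed.** Inputs: 60 nights and the 20% cut, hence more than 12 nights lost; 18% expected loss (Data Collection Quality Control; Results). Assumptions: quality-control losses count as missing data, nights are lost independently, and the cut applies to all 60 nights. Then P(cross) = P(Binomial(60, p) > 12).

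| Night loss p | P(cross) | Expected of 32 |
|---|---|---|
| 10% | 0.006 | 0.2 |
| 15% | 0.106 | 3.4 |
| 18% | 0.276 | 8.8 |
| 20% | 0.424 | 13.6 |

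At 18%, ending with 32 would mean randomising about 32 / (1 − 0.276) = 44. If loss varies between people (beta-binomial, correlation 0.05 to 0.10, assumed), the probability is about 0.35, or 11 of 32, and about 49 would be randomised.

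**3. Whether selection could matter.** A simulation with no true effect, 16 per arm after refilling, baseline correlation 0.6 and the planned one-sided ANCOVA (4000 runs) gave:

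- Exclusion unrelated to response: rejection rates of 0.048 to 0.056, so no harm to the nominal 5%.
- Exclusion in the experimental arm only made more likely by poor response: 0.09 to 0.18 for a log-odds slope of 1 per SD and 0.18 to 0.37 for a slope of 2, over base exclusion rates of 10% to 28%.

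The slopes are invented. The exercise shows direction and possibility and does not estimate this trial's bias.

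**4. Deletion against reporting.** For a participant who withdraws or is excluded, one section requires immediate deletion of the data. The harms section requires all adverse events in the final report, and Pilot Objectives requires retention and usable-night proportions. Applied literally, the first leaves the other two without complete, verifiable records for exactly these people.

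**The case against.** Several defences have force, and they limit what can be claimed.

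- **Blinding.** A reader might infer that both arms are open-label from day 30. Implementation and Blinding (Masking) Level say that control participants learn their group only at close-out. Before day 30 neither arm has been told or advised, so participants have little reason to drop out differently by arm in that period.
- **Outliers.** A reader might infer that participants with outlying scores are replaced. The phrase sits under sensor inaccuracies and may mean the device; Data Preprocessing Pipeline only flags outliers.
- **Allocation of replacements.** A reader might infer that newcomers are placed non-randomly in the depleted arm. The article does not say how they are allocated; taking the next place in the sequence is equally compatible.
- **Withdrawal for low scores.** Neither Concomitant Care Protocol nor Incidental Findings says that such participants are replaced, and the two differ on whether withdrawal is automatic.
- **Reporting.** A reader might infer that retention and harms cannot be reported at all. A headcount could survive deletion: Stopping Guidelines counts withdrawals, the harms section tracks them, and some harms go to the ethics committee. Data Preprocessing Pipeline also documents excluded nights and reasons.
- **Meaning of missing.** The 18% concerns quality-control exclusions, whereas the 20% cut is listed as user noncompliance. They may not be the same quantity.

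The article also treats all findings as hypothesis-generating. None of this supplies an analysis of all randomised participants, and the complete-plan statement rules out leaving it to a later document.

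**Conclusion.** The point stands in this form: the plan excludes and replaces participants after allocation, states no analysis of everyone randomised, ties the PSQI to watch completeness, and orders deletions that conflict with its own retention and harms commitments. The primary contrast is of a selected, refilled set. Bias is possible, chiefly through losses in days 31-60, but is neither shown nor quantifiable from the article. Outcome, retention and harms information on those removed would be incomplete or unverifiable.

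The scale of exclusion depends strongly on assumptions. About 28% of participants would cross the cut if the 18% loss counts as missing, nights are independent and the cut covers all 60 nights. The result is negligible at 10% loss and 42% at 20%. This should be corrected before the results are analysed.

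**What to change.** 1. **Primary analysis:** all randomised participants in their allocated arm, using available nights, with a prespecified minimum number of nights or weighting by nights, and a stated rule for a missing baseline mean. Keep the set with at least 80% of nights as a sensitivity analysis.
2. **Replacement:** replacements made after allocation must not substitute for randomised participants. Where they are already enrolled, include them as randomised, report them, and also count those whom they replaced.
3. **PSQI:** analyse everyone with day-0 and day-60 forms, whatever the watch data.
4. **Records:** subject to ethics approval and the consent terms, keep de-identified data up to exclusion, and always keep arm, reason and adverse events. Reconcile the deletion rule with Harms: Adverse Event Tracking and Pilot Objectives.
5. **Reporting:** give exclusions, replacements and lost nights by arm.
6. **Wording:** reconcile Adherence Assessment with Data Collection Quality Control on whether exclusion is optional, and Concomitant Care Protocol with Incidental Findings on withdrawal. State whether outliers lead to replacement of the device or of the participant.

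**Cost:** noisier means for participants with few nights, a final number possibly below 32, and an ethics amendment, because Protocol Amendments requires approval before ethical procedures change. Recruitment ended in July 2025 and data collection was due to finish by December 2025, so some replacements and deletions may already have happened. Deleted data cannot be recovered, and the loss should be disclosed.

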### Blinding (Masking) Level

This is an open-label pilot trial with partial blinding where feasible. Participants become aware of group assignment at different time points (experimental group participants are informed on day 30 at intervention delivery; control group participants are informed on day 60 at close-out). Samsung Galaxy Watch 4 automatically records objective sleep data independent of participant or researcher knowledge, eliminating measurement bias for the primary outcome. The researcher analyzing primary outcome data (Samsung scores) remains blinded to group allocation, and unblinding occurs on day 30 to identify participants for analysis in the experimental group in order to provide personalized recommendations.

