### Data Preprocessing Pipeline

Data are downloaded from Samsung Cloud onto the participant’s mobile device for transfer to the researcher’s computer for analysis. Moreover, individual nights are processed, sleep stages are integrated, and participant IDs are assigned. For quality control, nights with missing or corrupted segments are excluded, fragmented sleep data without combined scores are removed, daytime sleep (outside 7 PM to 11 AM) is excluded, nights with ≥30 minutes of stage/total discrepancies are excluded, and outliers >3 SD from baseline are flagged. For feature engineering, additional features (sleep stage percentage and real TST) are derived from the 10 device variables in ML analysis. Completeness of reporting is ensured by documenting the percentage of excluded nights and the reasons for exclusion.

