### Interim Analysis

No formal interim analysis is planned. The researcher conducts data quality monitoring but does not analyze outcomes until study completion to prevent bias.

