### Ancillary and Posttrial Care

#### Incidental Findings

Participants with incidental findings during the study may be withdrawn and referred for severe sleep deterioration (sleep score <30 for >1 consecutive week). Participants may be withdrawn from the study and referred to sleep medicine services at their medical institutions. Contact information may be provided for sleep specialists in Mexico City. There are no study-related costs for referral (participants use existing health insurance).

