### Anonymization Process (Deidentification)

Anonymization involves assigning an alias to the personal data collected from each participant at different process steps. Email or Samsung accounts do not use personal data. These accounts are only used for data collection, as the approach is already anonymous by design.

An alias is used at each phase of the process. The smartwatch user setup is generic, and the smartwatch collects objective data without the participant’s personally identifiable data. The same device and setup are used throughout the study. The pairing device setup, like the user setup, is generic, and thus, the mobile phone collects objective data without the participant’s personally identifiable data. PSQI questionnaire data collection uses the Participant_ID alias for subjective data collection without the participant’s personally identifiable data. In the last phase, the data are merged into a single dataset, which is one of the research outputs.

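### Outliers lead to replacement in one section but only to a flag in another; if participants are replaced, their data are deleted and the pilot understates variability

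*Protocol article*

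**What the plan says.** All references are to the Protocol article.

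- **Data Collection Quality Control:** "For sensor inaccuracies, quality control is performed through sleep diaries, and outliers trigger replacement". The next sentence reads "Excluded participants are replaced from the recruitment pool to maintain the sample size".
- **Data Preprocessing Pipeline:** nights are excluded for several listed reasons, but "outliers >3 SD from baseline are flagged".
- **Anonymization Process (Deidentification):** "The same device and setup are used throughout the study".
- **Blinding (Masking) Level:** "unblinding occurs on day 30 to identify participants for analysis in the experimental group". The same section says that the researcher analysing the primary outcome stays blinded.
- **Interim Analysis:** "The researcher conducts data quality monitoring but does not analyze outcomes until study completion to prevent bias".
- **Access Control and Protection Layers for Potential and Excluded Participants:** data of "those who voluntarily withdraw or need to be excluded from the study are immediately and securely deleted".
- **Safety trigger:** Concomitant Care Protocol states withdrawal and referral without qualification for a score under 30 lasting more than a week. Incidental Findings says that participants "may be withdrawn and referred for severe sleep deterioration (sleep score <30 for >1 consecutive week".
- **Pilot Objectives:** these include the size of the group difference, within-group variability and retention.

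**The concern.** The two outlier sentences prescribe different actions and nothing links them. If replacement is of participants, extreme recorded values can remove a randomized person from the trial. The rule has no time limit and does not exempt the sleep score, so it reaches the primary outcome window after the arm is known. Immediate deletion means that the removal cannot be examined or reversed later.

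The stake is the pilot's own product. Variability and effect size from this trial are meant to inform the sample size of a definitive one, and replacing extreme participants trims the tails of the distribution being estimated.

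The two versions of the safety rule raise a smaller, separate matter: it is unclear whether a deteriorating participant must be withdrawn and referred or only may be.

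**Working it through.** **1. Flag or replace.** The preprocessing sentence excludes nights for other reasons and uses a milder verb for outliers, so flagging there is a distinct action. The quality control sentence goes further. It is limited to sensor inaccuracies and names diaries as the check, but gives no criterion that separates a sensor fault from a genuinely extreme night.

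**2. What is replaced.** The next sentence replaces excluded participants, the missing-nights rule in the same section does too, and the anonymization text assumes one device throughout. Participants are therefore the natural reading. A watch is not ruled out in words.

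**3. Who knows what, and when.** The primary outcome covers days 31-60. The researcher learns the arm by day 30, and the Allocation Concealment Mechanism section suggests day 0. Data Management gives data access to the researcher alone, so no separate blinded person is visible. Outcome analysis is deferred, but data quality monitoring, where this rule operates, continues.

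**4. Size under the participant reading.** The plan states no figure to reproduce.

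Inputs from the plan: 16 per arm, analysis of covariance with one covariate, one-tailed alpha .05, residual df 32 - 3 = 29. Assumptions: normal residuals, no true effect, a random draw as replacement, and baseline-to-follow-up correlation r of 0.5 or 0.7. The table gives simulation results, which agree for both values of r.

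| Replaced | Mean shift (residual SD) | One-tailed rejection | Residual SD relative to no replacement |
|---|---|---|---|
| Nobody | 0 | about 5% | 1.00 |
| Most extreme 1 of 32, any arm or direction | 0 | about 5% | 0.92 |
| Most extreme 2 of 32, any arm or direction | 0 | about 5% | 0.87 |
| Lowest 1 in each arm | 0 | about 6% | 0.91 |
| Lowest 1, experimental arm only | +0.11 | about 10% | 0.96 |
| Lowest 2, experimental arm only | +0.19 | about 15% | 0.93 |

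Analytic check of the last two rows: the expected lowest and second-lowest of 16 standard normal values are -1.766 and -1.285. The shifts are 1.766/16 = 0.110 and (1.766 + 1.285)/16 = 0.191 residual SD. Multiplying by sqrt(1 - r²) gives 0.096 and 0.165 raw SD at r = 0.5, and 0.079 and 0.136 at r = 0.7.

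**5. What a smaller SD does downstream.** For a fixed difference in score points, sample size is proportional to SD². A relative SD of 0.92 gives 0.92² = 0.846, so a future trial would be planned about 15% too small. At 0.87, 0.87² = 0.757, about 24% too small. A standardized effect formed on that SD is inflated by 1/0.92 = 1.09 or 1/0.87 = 1.15.

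**6. How often.** This cannot be derived from the protocol. Suppose that one night beyond 3 SD sufficed and that nights were independent and normal. Then 1 - (1 - 0.0027)^30 = 0.078 per participant over days 31-60, or about 2.5 of 32. One or two replacements is thus not an extravagant number. The protocol does not say that a single night suffices, and a single-night trigger would select less sharply on the 30-night mean than the table assumes.

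**7. Safety rule.** Concomitant Care Protocol is unconditional. Incidental Findings is permissive and requires the week to be consecutive. A participant can meet one wording and not the other, and the action differs where both are met.

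**The case against.** The strongest reply is that the two sentences form a sequence: flag in preprocessing, check the diary, then act on a sensor fault, perhaps by swapping the watch. The sentence follows a list of device problems, and the same-device statement sits in a paragraph about aliases and account setup, so it does not forbid a swap. All of this is fair. If a watch is meant, the deletion argument falls away. But the protocol states neither the sequence nor what is replaced. It also says under Exploratory Analyses that it contains the complete statistical analysis plan and that no separate one exists, so the detail is not deferred elsewhere.

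A reader might infer that the plan lets the researcher discard poor experimental-arm results and so doubles or triples the false-positive rate. The documents do not support that. The rule names no arm, day or direction, the 3 SD flag is not restricted to low values, and outcomes are not analysed until completion. The 10% and 15% rates need one-sided removal from one arm, which no section describes. The Interpretation Guidance section also puts effect sizes and intervals ahead of significance.

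A reader might also infer that harms would go unreported. That is not supported either. Data Monitoring Oversight has adverse events monitored throughout, Harms has all of them reported, Stopping Guidelines need a withdrawal count, and the Accountability Framework triggers a review if experimental-arm scores worsen. The deletion rule does not forbid a tally.

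What stands is the missing link between flag and replacement, the deletion of randomized participants' data, the loss of SD, and the mismatch in the safety wording.

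**Conclusion.** The concern holds in limited form. Read as written, extreme values can lead to a randomized participant being replaced and the data destroyed, without a stated criterion for a device fault. Arm-neutral replacement leaves the mean difference unbiased and rejection at about 5%, but understates the residual SD by about 8% for one and 13% for two of the most extreme of 32 participants. That bears directly on a stated pilot objective. A mean shift of +0.11 to +0.19 residual SD is a worst case and should not be presented as what the plan provides for.

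These figures rest on the participant reading, normal residuals, random replacement and an assumed number of removals. The safety mismatch is small but real. Confidence is medium, because the object of replacement is not named.

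**What to change.** 1. In Data Collection Quality Control, flag outliers as in Data Preprocessing Pipeline and keep the participant in the analysis. Exclude nights or swap a device only for a fault confirmed by diary or device check, never for an extreme score alone. Record any swap.
2. Word the safety rule identically in Concomitant Care Protocol and Incidental Findings. The threshold of 30 and the clinical action are for the sponsor to settle.
3. Exempt from the deletion rule a non-identifying log of arm, study day and reason for every randomized participant withdrawn, excluded or replaced, and report it by arm.

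The cost is wording in these sections, a short log, and ethics committee approval before implementation as Protocol Amendments requires. No visits or measurements are added. Recruitment ended in July 2025 and deletion is immediate, so entries for participants already removed may not be recoverable. If so, the report should say so.
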